### Study measures

Data will be collected to assess the primary and secondary study outcomes as well as mediation/moderation measures to evaluate the impacts of the intervention. Table 7 shows the measurements and assessment timelines for the study. We have selected the measures that have established validity and reliability in the study population. All measures for the parents are offered in English and Spanish. To increase parental participation and compliance with assessment protocol, we will provide incentives (up to $30) that are linked to returning daily food/screen time/sleep logs ($3/d) and parent surveys ($9 and raffles for tricycle) at each assessment time. Prior to each data collection, we will provide training on data collection protocols, including privacy protections, to all assessment staff..

**Table 7 Tab7:** Study measures and assessment timelines

Primary outcomes	Baseline	Posttest	Follow-up
Height, weight, Body Mass Index (BMI; kg/m^2^); BMI z-score [59]	C	C	C
Secondary outcomes			
7-day accelerometry for PA, sedentary time and sleep [60]	C	C	C
The Test of Gross Motor Skills	C	C	C
Aggregated plate waste test^,^ (241)	C	C	C
National Health and Nutrition Examination Survey (NHANES) Dietary Screener			
7-day logs for child screening and sleep time (min/d) [61]	P	P	P
Computer-assisted pictorial test for food preferences [62]	C	C	C
Mediator/moderator measures			
The Home Self-administered Tool for Environmental Assessment of Activity and Diet [63]			
The Parenting Strategies for Eating and Activity Scale [56]	P	P	P
Parent health knowledge test [43]	P	P	P
Parental confidence/self-efficacy scale [64]	P	P	P
Food Behavior Checklist [65]	P	P	P
Acculturation scale [66–68]	P		
Parent weight and physical activity [69]	P	P	P
Family socio-demographics/health history	P		

Data source: *C* child, *P* parent, *S* staff

The primary outcome of the study is child’s BMI calculated as weight in kilograms divided by height in meters squared. Child’s height and weight will be measured twice at the beginning of the school day with no shoes and light clothes, using a stadiometer and digital weight scale. Discrepancy between the two measures must be ≤0.5 cm and ≤ 0.25 kg. We will measure every fifth child by two staff to assure the accuracy and reliability of the weight and height measures.

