#### Data analysis plan

For Hypothesis 1, we will first calculate the change in BMI at T1 from T0 and at T2 from T0 for each child. We will then compare the difference in change scores among the three intervention groups using ANOVA test or Kruskal-Wallis test at each time point separately. Multiple comparisons defined by various linear combinations of groups (i.e., CBI-control; C&HBI-control) will be performed to exam the difference in change scores with Bonferroni adjustment. To utilize all three measures from each child, generalized linear mixed effects models (GLMMs) will be used to examine the group differences at different time points with BMI as the response variable, and time (3 levels: T0, T1 and T2) and group (3 levels) and their interaction as the explanatory variables. Two random effects will be included in a GLMM: one to account for the correlation among children nested within the same center, and one to account for the three repeated measures of each outcome within the same child. Center size and cohort, as fixed effects, will be included in the model as well. We will also include baseline BMI, child gender and race/ethnicity, and other covariates (e.g., parent characteristics and health behaviors) in the model as needed. Model fit will be assessed by residual diagnostics [81] to guide the best fit model. For Hypothesis 2, we will use the same statistical procedure for testing Hypothesis 1 to analyze the secondary outcome measures (i.e., MVPA, sedentary behavior, TV watching, sleep, and dietary measures), with baseline BMI as a covariate as well to check for differential effect of intervention associated with children’s level of adiposity. When there are missing data, we will compare the dropouts and completers on demographics and various outcome measures using available data. If data are missing at random (MAR) [82], standard computational algorithms such as EM implemented in statistical software allow the use of all the data available to generate appropriate parameter estimates. If the MAR assumption is in doubt, we will conduct sensitive analysis to impute missing data using the multiple imputation with chained equations approach [83]. Specifically, we will impute missing values by adjusting for time of measurement and demographics to create 10 imputed datasets. We will then combine the effect sizes using the Rubin’s rules [84]. Stata/SE (version 15, College Station, Texas) or SAS (version 9.3, Cary, North Carolina) will be used for conducting all analyses proposed.

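### The Hypothesis 2 outcomes are analysed as raw change without conditioning on each outcome's own baseline value, which is valid but less precise than the data allow and sensitive to chance baseline imbalance

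*Protocol article*

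**What the plan says.** In the Protocol article, the Data analysis plan states that for Hypothesis 2 the Hypothesis 1 procedure will be used "to analyze the secondary outcome measures (i.e., MVPA, sedentary behavior, TV watching, sleep, and dietary measures), with baseline BMI as a covariate as well". The Hypothesis 1 procedure has two steps.

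- **Change scores.** T1-T0 and T2-T0 are computed per child. The plan will then "compare the difference in change scores among the three intervention groups using ANOVA test or Kruskal-Wallis test at each time point separately". No covariate enters this step.
- **Mixed model.** The response is the outcome at all three visits, with "time (3 levels: T0, T1 and T2) and group (3 levels) and their interaction as the explanatory variables". One random effect is for center and the other is "one to account for the three repeated measures of each outcome within the same child". Center size and cohort are fixed effects. Baseline BMI, gender, race/ethnicity and other covariates are added as needed.

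For Hypothesis 2 the plan adds one named baseline variable, "with baseline BMI as a covariate as well to check for differential effect of intervention associated with children’s level of adiposity".

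Table 7 (Study measures) shows that own baselines are collected for several outcomes, for example "7-day accelerometry for PA, sedentary time and sleep [60] C C C". The gross motor test, the food preference test and the screen/sleep logs are also marked at all three visits. The Mediation analysis section names a baseline measure as a possible covariate. The Hypothesis 2 text does not.

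**The concern.** A raw change score fully subtracts the baseline. That is efficient only when T0 and T1 correlate near 1. When the correlation is lower, the subtraction adds baseline noise to the contrast and over-corrects any chance difference between arms at T0. A week of accelerometry or parent logs, repeated 7 or 21 months later, need not correlate closely with the first reading, and the protocol gives no figure.

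At stake is Aim 2. With 4 centers per arm, arms may differ by chance in activity or sleep at T0. An arm that starts better on a desirable behaviour is then penalised by the change score, and real behavioural effects carry wider intervals than the same data could give.

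**Working it through.** **Inputs from the protocol (Power and sample size):** 4 centers per arm, 29 children per center, two-sided 5%, difference 0.53, SD 1.147, intraclass correlation 0.003. These concern BMI; no power or intraclass correlation is stated for the secondary outcomes. **Assumed:** r, the T0-T1 correlation of a secondary outcome, shown from 0.3 to 0.9.

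**1. The plan's own figure.** Design effect = 1 + 28 × 0.003 = 1.084. SE = 1.147 × √(1.084 × 2/116) = 0.157. Noncentrality = 0.53/0.157 = 3.38. A noncentral t with 2 × (4 − 1) = 6 df gives power 80.3%, so the stated 80% reproduces. It serves below only as a reference layout.

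**2. Does the mixed model differ from the change score?** With complete data and T0 unconstrained, no. In a simulated data set the T1 group-by-time estimate was 0.1586, identical to the raw difference in change. Adding baseline BMI left the estimate at 0.1586 and the SE at 0.1911. In a second data set (12 centers of 29, r = 0.5), the outcome's own T0 value entered as a main effect also left the estimate unchanged. A covariate that is constant over time cannot move a within-child contrast when T0 is itself a response.

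**3. Precision.** With equal variance s² at both visits, Var(change) = 2s²(1 − r) and Var(own-baseline ANCOVA) = s²(1 − r²). Their ratio is (1 − r²)/(2(1 − r)) = (1 + r)/2. The extra children needed by the change score are 2/(1 + r) − 1. The power columns take an effect that change scores detect with 80% power (6 df) and recompute its power under ANCOVA, with the intraclass correlation equal on both scales.

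| r | Variance ratio | Extra children for change score | ANCOVA power, 6 df | ANCOVA power, 5 df |
|---|---|---|---|---|
| 0.3 | 0.65 | 54% | 93% | 91% |
| 0.5 | 0.75 | 33% | 90% | 87% |
| 0.7 | 0.85 | 18% | 86% | 83% |
| 0.8 | 0.90 | 11% | 84% | 81% |
| 0.9 | 0.95 | 5% | 82% | 79% |

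**4. Clustered simulation** (2,000 runs, two arms of 4 centers of 29, assumed intraclass correlation 0.01 with center effects that stay the same from T0 to T1, assumed BMI-outcome correlation 0.1). The SDs of the group estimate were:

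| r | Change | Change + baseline BMI | Own-baseline ANCOVA | Variance ratio |
|---|---|---|---|---|
| 0.3 | 0.1555 | 0.1555 | 0.1361 | 0.77 |
| 0.5 | 0.1355 | 0.1359 | 0.1205 | 0.79 |
| 0.7 | 0.0977 | 0.0979 | 0.0940 | 0.93 |

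The gain is smaller than in step 3 because a stable center effect cancels in the change score. These ratios turn 80% power into about 89%, 88% and 83% with 6 df, and about 86%, 85% and 80% with 5 df.

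**5. Chance imbalance.** In SD units, the SD of the arm difference at T0 is √(1.084 × 2/116) = 0.137 at intraclass correlation 0.003, and √(1.28 × 2/116) = 0.149 at 0.01 (design effect 1 + 28 × 0.01 = 1.28). Mean estimates in the simulation were within 0.006 of the true 0, so there is no bias over randomizations. The slope of the change-score estimate on the T0 imbalance was −0.54, −0.41 and −0.21 at r = 0.3, 0.5 and 0.7, against +0.15, +0.08 and +0.08 with own-baseline adjustment. At r = 0.5, an imbalance of 0.2 SD moves the change-score estimate by about −0.41 × 0.2 = −0.08 SD.

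**The case against.** **The text leaves room for own-baseline adjustment.** Other covariates may enter as needed, and under Hypothesis 1 the named baseline covariate is the outcome's own. The article condenses a fuller plan, and a final covariate list can wait for it. This stands as far as covariate choice goes. It does not remove the point: by step 2, no time-constant main effect alters the contrast of the model that is written down. The model structure has to change.

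**A reader might infer that baseline BMI is used as a substitute for the outcome's own baseline.** The text does not say so. BMI is added as well, for a stated effect-modification purpose, and each outcome's T0 value is used, in the change score and as a response.

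**A reader might infer that regression to the mean biases the estimates.** Under randomization it does not, as step 5 shows. It matters only given a chance imbalance.

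**The size is uncertain.** This stands. No r is documented, the 80% starting power is borrowed from BMI, the ratio (1 + r)/2 carries over to center means only if the intraclass correlation is alike on both scales, and step 4 shows smaller gains when it is not.

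**Not every outcome has a child-level baseline.** This also stands. The plate waste test is aggregated, and Table 7 as available does not clearly show a per-child T0 value for dietary intake. Gross motor skills are in Hypothesis 2 and Table 7 but not in the list of measures in the Data analysis plan.

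**The mediation analysis** already allows for a baseline measure, so no harm is claimed there.

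**Conclusion.** The point holds as one of efficiency and robustness, not of validity. As written, both steps for Hypothesis 2 reduce, with complete data, to the raw difference in change (by ranks if Kruskal-Wallis is used), and baseline BMI adds nothing to its precision. Conditioning on own T0 would cut the variance to 0.65, 0.75 or 0.85 of its value at assumed r of 0.3, 0.5 or 0.7, or to 0.77, 0.79 or 0.93 if center effects are stable at an intraclass correlation of 0.01. It would also largely remove the dependence on chance T0 imbalance. At r of about 0.7 to 0.9 the gain can be nil if a center-level degree of freedom is lost. The change is worth making, because it costs little and Aim 2 rests on few centers.

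**What to change.** In the Hypothesis 2 text, for each secondary outcome with a child-level T0 value, make one of these the main analysis:

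- a center-clustered mixed model of the T1 and T2 values, with group, time and group-by-time, and with the outcome's own T0 value and its interaction with time as covariates; or
- the three-visit model with arm means constrained to be equal at T0.

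This covers accelerometry (physical activity, sedentary time, sleep), the screen/sleep logs, gross motor skills and food preferences. It covers dietary intake only if that is measured per child at T0. Add gross motor skills to the listed measures. Keep baseline BMI with a BMI-by-group term, which is what the stated differential-effect check needs.

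The cost is one or two sentences and no new data. There are two downsides: possibly one center-level degree of freedom, and the need for the constrained-baseline form to retain children without a T0 value.

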
#### Mediation analysis

We will test for mediation effects following the 4-step procedures outlined by MacKinnon et al. [85] to investigate the behavioral pathways between the intervention and outcomes as depicted in Fig. 1 (i.e., if the intervention worked as designed) using structural equation models [86]. A series of GLMMs will be conducted to examine if the strength of the association between the intervention and each outcome of interest is modified when controlling for each mediator. Specifically, we will test the direct and indirect effect of intervention on study outcomes (i.e., child BMI and secondary outcome measures) through each mediator (i.e., intra- and inter-personal and environmental variables) adjusting for covariates (e.g., demographics and baseline measure) as appropriate.

#### Cost-effectiveness (CE) analysis

We will conduct a trial-based analysis to estimate the CE of *¡Míranos!* compared to no intervention, following standard methods for economic evaluation [87]. Three treatment approaches will be compared based on direct observation of the impact of *¡Míranos!* on cost and effect (i.e., BMI): 1) CBI + HBI; 2) CBI; and 3) control. The economic evaluation will be conducted from the perspective of the program provider. We will use the ingredient approach to estimate the program delivery costs incurred in implementing *¡Míranos!*, which multiplies units of resource utilization with unit costs [88]. Resource utilization and unit costs for the program perspective will be measured by collecting information on: 1) food preparation records and PA equipment; 2) delivery of classroom activities; 3) delivery of HBI; and 4) staff training including peer parent educators and monetary incentives per school. Net intervention costs will be calculated by subtracting usual program costs in absence of the intervention from the intervention costs. All costs will be discounted at 3% per annum where applicable and will be expressed in 2018 U.S. dollars. The CE will be calculated based on mean BMI reduction for each approach using the individual-level data. The cost and health outcome of each approach will be synthesized to calculate incremental CE ratios (in terms of net intervention cost per unit BMI reduction) compared to the next effective approach. Any dominated or weakly-dominated strategy will be excluded. Sampling (or stochastic) uncertainty inherent in the trial-based economic evaluation will be evaluated using cost-effectiveness acceptability curves (CEACs), which estimate the probability that an intervention would be cost-effective under varying ranges of willingness-to-pay thresholds for a unit reduction in BMI. CEACs will be constructed using nonparametric bootstrapping with 2000 replicates [87]. STATA 14 for Windows (StataCorp LP, College Station, Texas) or SAS (version 9.3, Cary, North Carolina) will be used for conducting the bootstrap analyses.

### Plan for dissemination

In addition to publications and professional presentations on study outcomes, we plan to create a dissemination package of the *¡Míranos!* intervention that includes: 1) manuals describing intervention components; 2) procedures and resources for implementation and evaluation; 3) fixed costs, variable costs, and CE associated with the intervention; 4) staff training modules; and 5) the intervention’s feasibility and acceptability to inform others in their decisions for adoption [89]. We also plan to work with the National Head Start Association, YMCA, and other childcare organizations to facilitate the translation of *¡Míranos!* into real-world settings if it is shown to be efficacious in the proposed study.

### Data management plan

Study data will be stored in a secured database. All data collection forms will be processed and stored in a secured location. Research staff will enter collected data into the database. Data collection forms will be reviewed immediately after collection for missing or ambiguous information so that clarification or corrections can be made promptly. Data entry quality control will be performed following the double data entry procedure. Quarterly quality control reports will be reviewed and remediation (e.g., re-training) will occur promptly as needed.

### Data safety and monitoring

Because this study is a behavioral intervention of minimal risk, the data safety and monitoring will be performed by an independent monitor. Participants accrual (adherence to protocol regarding demographics, inclusion/exclusion) and retention will be reported at the end of each data collection wave. Compliance to intervention protocol and adverse event rates will be reviewed quarterly. The stopping rules that might be relevant would be: 1) study recruitment or retention becomes futile; or 2) any new information concerning PA and dietary recommendations or safety becomes available during the trial that necessitates stopping the trial. We have no plan to perform interim data analysis.

## Discussion

To our knowledge, the *¡Míranos!* intervention is the first preschool obesity prevention study using an integrated approach to address multiple EBRBs in multiple settings in low-income young children in the United States. The design of the study is informed by recent childhood obesity prevention interventions with considerations of programming and methodological issues identified in the literature [90, 91]. Many of these studies, however, were conducted in Australia and European countries. This study will provide much needed information on the cost-effectiveness of an obesity prevention program in a U.S. child care setting.

The design of this study has several important strengths and weaknesses that may influence the validity and generalizability of the study findings. First, this is a clustered RCT with a long-term follow-up assessment that is made possible by the commitment and support of two Head Start organizations. Findings from this study will provide answers to many questions on the impacts of a multi-faceted intervention targeting both the childcare and home environment. Second, *¡Míranos!* CBI will implement a comprehensive set of center policies and staff training that will address many of the enablers and barriers in a childcare setting. The feasibility and acceptability of these evidence-based policies will be critically examined by the process evaluation data. Previous RCT studies have not provided detailed evaluations of these critical issues in a childcare setting. Third, the intervention activities are tailored to address the barriers facing children and families living in low-income and predominantly Latino communities. A lack of cultural tailoring has been identified as a limitation in previous studies. Finally, *¡Míranos!* intervention is grounded in social cognitive and behavioral theories. This study will test the influences of mediators and moderators on the study outcomes based on the intervention model.

The limitations of the study include the problem of concealment. The Head Start staff are not blinded to the treatment assignment. Concealment of the assignment is not possible because of the need to plan intervention logistics with the administrative staff and conduct the staff training before the start of the school year. It is not clear how staff participation will be biased by this practice. We purposefully enhanced the program for the comparison centers to include the provision of the IMIL program and a parent literacy education program. We hope that the use of an active control program will increase the appeal to the comparison participants and retain them in the study. Another limitation is that the data collection staff will also not be blinded to the treatment assignment. This is especially true for the assessment of the second cohort participants since all of the intervention centers will have many visible signs of *¡Míranos!* intervention. We will address this weakness by conducting a standardized protocol of assessment and close monitoring of the measurement of the primary outcome.

Early childhood obesity is a complex health problem especially among low-income and minority children. There is currently limited evidence on effective prevention strategies based on RCTs in this age group. Designed as an efficacy study, the *¡Míranos!* intervention has been tailored for low-income, Latino preschool children and parents following recent recommendations and guidelines for obesity prevention targeting childcare and home environments. As such, the proposed study can contribute to the evidence base on this important public health concern.

## Abbreviations

¡*Míranos*: ¡*Míranos*! Look at Us, We Are Healthy!
BMI: Body Mass Index
BMI-percentile: BMI-percentile for age and gender
CACFP: The Child and Adult Care Food Program
CBI: Center-based intervention
CE: Cost-effectiveness
CEACs: Cost-effectiveness acceptability curves
EBRBs: Energy-balance-related behaviors
GLMMs: Generalized linear mixed effects models
HBI: Home-based intervention
HHL: The Sesame Workshop bilingual Healthy Habits for Life
IMIL: I am moving, I am learning
MAR: Missing at random
MVPA: Moderate to vigorous physical activity
PA: Physical activity
RCT: Randomized controlled trial
T0: Baseline
T1: Immediate post-intervention
T2: 1-year post-intervention follow-up
U.S.: The United States
UTSA: The University of Texas at San Antonio
zBMI: BMI z-scores for age and gender
